## Abstract

**Background:**

Insomnia is a common sleeping disorder which affects the quality of life which can bring harms to physical and mental health of human beings and even economic development. Traditional Chinese medicine (TCM) plays an outstanding role in treating chronic diseases and alleviating their symptoms. Therefore, the purpose of this study is to assess the treatment efficacy in patients with insomnia treated with abdomen-rubbing qigong exercise (ARQE). In addition, the brain function changes of patients will be explored by resting state functional magnetic resonance imaging (rs-fMRI).

**Method/design:**

This trial is a randomized, single-blind, controlled study planned to transpire between July 1, 2020, and July 31, 2021. A sample size of 114 participants (57 per group) with chronic insomnia will be randomly assigned to receive ARQE or CBTI for 8 weeks. The study duration will be 13 weeks, including a 1-week screening period, 8 weeks of intervention, and another 4 weeks of follow-up. The primary outcome is the Pittsburgh sleep quality index scores. Secondary outcomes include insomnia severity index, gastrointestinal symptom rating scale, the Hamilton Depression Scale, and rs-fMRI scan. The adverse events will be in control.

**Discussion:**

The results of this study will help to clarify the efficacy of ARQE in the treatment of insomnia and try to use rs-fMRI technology to explore the brain function changes of ARQE in improving sleep quality in patients with insomnia disorder. If the results are as expected, this study will provide high-quality evidence for the treatment of insomnia with ARQE.

**Trial registration:**

China Clinical Registration Agency ChiCTR1900028009. Registered on 19 December 2019.

## Background

Chronic insomnia refers to a sleeping disorder characterized by frequent or persistent difficulty in falling asleep or staying asleep [1]. Therefore, patients with insomnia hardly feel satisfied with their sleep quality [2]. Insomnia is a worldwide problem. Researches show that the incidence rate in Japan is 37.2%, in the USA is 27.1%, and in China is 15.0% [3, 4]. Insomnia can lead to daytime sleepiness, impaired attention, memory and other cognitive functions, reduced quality of life, and increased risk of medical conditions such as high blood pressure, depression, and anxiety [5–11]. The economic cost of insomnia is enormous, with an estimated of $30 billion to $35 billion spent on insomnia annually in the USA [12]. In conclusion, chronic insomnia is a serious illness which can bring harms to physical and mental health of human beings and even economic development.

Hypnotics and sedatives can relieve the symptoms of insomnia to some extent, but there are risks of adverse reactions and drug addiction. Cognitive behavior therapy of insomnia (CBTI) can change patients’ wrong sleep cognition and behavior, rebuild proper sleep cognition mode, and improve sleep mode [13–15]. It is considered as the cornerstone therapy in insomnia treatment. However, due to the insufficient number of CBTI psychiatrists/psychologists who are well trained in treating insomnia, also only a few patients can afford the treatment bills [16, 17]. Therefore, it is necessary to explore a more economic intervention for patients with insomnia.

The abdomen-rubbing qigong exercise (ARQE) has a long history of treating insomnia in China, which also named “nine rotating methods to prolong life,” summarized by the famous Qing dynasty medical practitioner Fang Kai in China [18]. It was first recorded in the “Nei Gong Tu Shuo” published in 1881 [19]. In China, abdominal massage has been widely used in the treatment of chronic diseases such as digestion diseases and insomnia [20]. Tan’s research shows that abdominal massage can significantly increase the insomnia patient’s total sleep time and lower the PSQI score [21]. ARQE is often used in the clinic of our research group; we found that this intervention is proved to be able to improve not only sleep quality but also gastrointestinal function, which are strongly connected. The beneficial effect of ARQE in chronic insomnia is widely known, but there have been no large-scale randomized controlled trials of efficacy and safety of ARQE treatment and lack of high-quality evidence for the treatment of insomnia with ARQE.

Chronic insomnia is a typical psychosomatic disease, which not only has a negative impact on physical health, but also has a certain impact on the patient’s psychology. Patients with chronic insomnia are often accompanied by emotional disorders such as excessive thinking, anxiety, depression, abnormal feelings, consciousness, emotions, and cognitive functions. Over time, pathological changes in brain structure and compensatory changes will occur [22]. Rs-fMRI (resting-state functional magnetic resonance imaging) study may help in elucidating the brain’s intrinsic functional organization to aid in understanding the brain function changes of insomnia and its treatment. Functional connectivity (FC) and amplitude of low-frequency amplitude (ALFF) are two methods of rs-fMRI analysis. In previous rs-fMRI studies, compared with healthy people, insomnia patients often have abnormalities in part of the brain functional activities and functional connectivity of brain regions. These abnormal areas are mainly concentrated in the prefrontal lobe, hippocampus, temporal cortex, and anterior cingulate [23–25].

Therefore, we aim to conduct a randomized controlled clinical trial of ARQE treatment for chronic insomnia to certify the efficacy of ARQE in the treatment of insomnia and try to use rs-fMRI technology to explore the changes in brain function of ARQE in improving the sleep quality of insomnia patients.

## Method and design

### Study design

To evaluate the efficacy of ARQE, a clinical randomized controlled trial is designed, with both evaluators and participants blinded to the design. In this trial, the participants are randomly divided into ARQE group and CBTI group, with 57 people in each group. Informed consent will be required for study participation. In addition, all researchers will be required to sign the commitment to protect the confidentiality of study participants. The purpose of the study and possible risks (such as adverse clinical outcomes and treatment-related adverse events) will be informed to every patient. Signed and dated consent forms will be required from those who agree to share their clinical data with the participating hospitals or regulatory agencies. All concomitant care and interventions are permitted other than concomitant receipt of any other experimental treatment. The details are shown in Fig. 1 and Table 1. This SPIRIT checklist is described in detail in additional file 1.

**Fig. 1 Fig1:**
[figure not shown]
Neuroimage and clinical data analysis

**Table 1 Tab1:** Schedule for enrollment, intervention, and assessment

Activity	Phase (time point)	Screening/enrolment (week0)	Allocation	Treatment/intervention								Follow-up
				Weeks 1	Weeks 2	Weeks 3	Weeks 4	Weeks 5	Weeks 6	Weeks 7	Weeks 8	Weeks 12
Enrolment	Eligibility screening	√										
	Acquisition of informed consent	√										
	Clinicopathological evaluation	√										
	Enrolment	√										
	Random allocation		√									
Treatment/intervention	Abdomen-rubbing qigong exercise			√	√	√	√	√	√	√	√	
	Cognitive behavioral therapy for insomnia			√	√	√	√	√	√	√	√	
Outcome assessment	PSQI	√					√				√	√
	ISI	√					√				√	√
	GSRS	√					√				√	√
	HAMD	√					√				√	√
Safety observation	fMRI	√									√	
	Adverse event			√	√	√	√	√	√	√	√	√
	drug combination			√	√	√	√	√	√	√	√	√

### Participants

#### Recruitment strategy

Participants will be recruited through advertisement and referrals starting in July 1, 2020. There are three main strategies for recruiting insomniacs. The first strategy was to recruit participants from the outpatient and inpatient departments of Yueyang Hospital of Integrated Traditional Chinese and Western Medicine affiliated to Shanghai University of Traditional Chinese Medicine. Second, printed recruitment posters will be distributed at the Shanghai university of traditional Chinese medicine and in nearby communities to recruit potential research subjects. Third, we will advertise our research through the Internet and social media (e.g., WeChat) to attract patients who may be willing to participate.

#### Sample size calculation

The required sample size is calculated using an estimation formula based on the difference between two sample means and standard deviations (Pittsburgh Sleep Quality Index, which is assessed using composite points of sleep quality). A previous clinical study suggests that the mean and standard deviations of Pittsburgh Sleep Quality Index (PSQI) in ARQE group(*n* = 40) after treatment are 8.45 and 2.06, while the mean and standard deviations of PSQI in CBTI group (*n* = 40) after treatment are 9.92 and 2.65 [26, 27]. The sample size is calculated in the following formula, with the two-sided significance level (α) set at 0.05 and statistical power at 0.80 [28]. Thus, a minimum sample size of 51 participants per group (102 participants in total) is calculated to provide sufficient statistical power to detect a between-group mean difference of 1.47 in treatment efficiency, defined as the change in PSQI score.

Considering a 10% loss to follow-up, we aim to recruit 57 patients in each group, in a total of 114 patients. According to fMRI studies, 15 to 30 patients are adequate to test hypotheses.

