### Randomization

Included participant will be randomly divided into the ARQE group and the CBTI group according to a 1:1 ratio. Block randomization is used with 4 block size to generate two different sets of random numbers lists. Random number tables are generated by researchers who have no contact with participants or evaluators. Each random number is sealed in a pre-prepared opaque envelope with the patient’s serial number on it. After the participant has been certified and signed a written informed consent, participant will open an envelope with patient serial number is opened and know the group of participant belongs to. Informed consent is available by email to corresponding authors. Because of the significant difference between massage treatment and CBTI, double-blinded method cannot be used. Thus, it is important to ensure the data analyst does not know the grouping and intervention method of the insomnia patients.

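### The trial is sized on post-treatment PSQI scores, but the stated power is attached to change in PSQI, for which no SD is given and 80% is not assured

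*Protocol article*

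**What the plan says.** All of the sizing is in the protocol article, under Sample size calculation. The ARQE mean and SD "after treatment are 8.45 and 2.06"; the CBTI mean and SD "after treatment are 9.92 and 2.65". The test has "two-sided significance level (α) set at 0.05 and statistical power at 0.80". The result is given as "a minimum sample size of 51 participants per group (102 participants in total) is calculated to provide sufficient statistical power", and the sentence goes on "to detect a between-group mean difference of 1.47 in treatment efficiency, defined as the change in PSQI score". The dropout step follows: "Considering a 10% loss to follow-up, we aim to recruit 57 patients in each group, in a total of 114 patients". Allocation is 1:1 (Randomization).

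The section refers to a formula that is not in the text at hand, and the surviving text does not say whether one arm's SD or both entered it.

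The Primary outcome section gives the endpoint as the PSQI score, measured at weeks 0, 4, 8 and 12, and does not mention change. Under Primary outcome analysis, the between-group tools are a t test or a non-parametric test, together with repeated-measures ANOVA with a group-by-time interaction. Adjustment for baseline PSQI is not mentioned.

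**The concern.** The difference of 1.47 is the gap between two end-of-treatment means, and the only SDs given are SDs of end-of-treatment scores. The section nevertheless claims its power for a change score. Under randomisation the expected between-arm difference is the same for both, so 1.47 can serve as the target either way. The variance is not the same. The SD of a change score depends on how strongly baseline and post-treatment PSQI correlate, and the protocol gives neither that correlation nor an SD of change.

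This paragraph is the article's only justification for 114 participants. If change is what gets tested, the 80% has no support in the printed figures, and true power could be well below it. Two SDs are printed and only one of them reproduces 51, so a reader also cannot tell which variance assumption the stated power rests on.

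**Working it through.** **Inputs** (Sample size calculation): means 8.45 and 9.92, SDs 2.06 and 2.65, two-sided alpha 0.05, power 0.80. The difference is 9.92 − 8.45 = 1.47, exactly the printed value, so it is a difference in post-treatment means.

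**Step 1. Reproduce 51.** With one common SD, n per group = 2 × (z₁ + z₂)² × SD² / difference².
- SD 2.65, z-values 1.960 and 0.842: 2 × 2.802² × 2.65² / 1.47² = 51.01.
- SD 2.65, z-values rounded to 1.96 and 0.84: 2 × 2.80² × 2.65² / 1.47² = 50.96, which rounds up to 51.
- Dropout: 51 / 0.90 = 56.7, so 57, as printed.

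The larger SD in both arms therefore gives the protocol's figures. Power at 51 per group on that basis is 80.0% by the normal approximation and 79.2% by the t test.

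**Step 2. Use both printed SDs.** n = (z₁ + z₂)² × (SD₁² + SD₂²) / difference² = 2.802² × (2.06² + 2.65²) / 1.47² = 40.92, so 41 (42 by the t test). The pooled SD is √((2.06² + 2.65²)/2) = 2.373. On this basis 51 per group gives about 87% power and 57 gives about 91%.

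**Step 3. Power if change is analysed.** Assume equal baseline and post-treatment SDs and correlation r. Then SD of change = SD × √(2(1 − r)). For example, at SD 2.65 and r = 0.3 it is 2.65 × √1.4 = 3.14. The t-test power for 1.47 points at 51 per group is:

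| Assumed r | SD of change (from 2.65) | Power | SD of change (from 2.373) | Power |
|---|---|---|---|---|
| 0.3 | 3.14 | 65% | 2.81 | 74% |
| 0.5 | 2.65 | 79% | 2.37 | 87% |
| 0.7 | 2.05 | 95% | 1.84 | 98% |

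At r = 0.5 the SD of change equals the SD of the score, so the two analyses have the same power. Below 0.5 change is the weaker analysis; above it, change is stronger than the unadjusted post-treatment score.

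**Step 4. Power if week-8 PSQI is adjusted for baseline.** Under the same assumptions the residual SD is SD × √(1 − r²). At SD 2.65 and 51 per group:
- r = 0.3: residual SD 2.65 × √0.91 = 2.53, power about 83%.
- r = 0.5: residual SD 2.65 × √0.75 = 2.29, power about 89%.
- r = 0.7: residual SD 2.65 × √0.51 = 1.89, power about 97%.

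At each of these correlations the power exceeds that of both the unadjusted post-treatment comparison (79%) and the change score.

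**The case against.** The strongest reply is that the calculation is sound and the fault is one loose clause. Much of that stands. Taking the larger SD for both arms is a standard conservative choice, and it gives 51. The formula may have shown this and been lost when the text was extracted. The Primary outcome section already names the PSQI score, which matches the inputs, and on that endpoint the trial meets or exceeds its stated power.

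Two stronger readings are tempting, and the documents do not support either:
- A reader might infer that the inputs give 41 per group and that 51 is a miscalculation. But 41 is the answer only when both SDs are used, and the surviving text does not rule out the other choice.
- A reader might infer from the paired citation that the two means come from separate studies, so that 1.47 is not a within-study contrast. The text speaks of a single previous study, and two references can describe one study. The sources are not at hand, so this cannot be settled.

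It can also be said that power well under 80% for change needs the larger SD together with a low correlation. That is fair: at the pooled SD, change has about 74% power at r = 0.3 and 87% at r = 0.5.

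What does not stand is that the clause is harmless. It is the sentence that says what the power is for. The planned group-by-time interaction also asks whether the arms change differently over the visits, so a change-type analysis is a live possibility.

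**Conclusion.** The point holds as a mismatch between the endpoint sized and the endpoint named, with an unnamed SD beside it. The 80% is supported for a post-treatment PSQI score at a common SD of 2.65. It is not supported for change, where power at 51 per group lies anywhere between 65% and 98% across the cases in the table. That range rests on assumed correlations of 0.3 to 0.7 and on equal baseline and post-treatment SDs, neither of which the protocol gives. The enrolment target of 57 per group is not in question. The correction is worth making because it settles what the power refers to, and because baseline adjustment raises power without adding participants.

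**What to change.** Keep 57 per group and make three changes.

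1. In Sample size calculation, replace the reference to change with the week-8 PSQI score. Week 8 is the end-of-treatment visit, so it matches the post-treatment inputs. Name the same endpoint and visit under Primary outcome.
2. State the basis, for example: 51 evaluable participants per group give about 80% power, at two-sided alpha 0.05, to detect a 1.47-point difference in week-8 PSQI, assuming a common SD of 2.65 (the larger of the two cited SDs) and before any baseline adjustment.
3. Under Primary outcome analysis, make the primary between-group comparison an ANCOVA of week-8 PSQI adjusted for baseline PSQI, in place of an unadjusted t test or a change score.

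The cost is a text amendment. Baseline and week-8 PSQI are already in the assessment schedule, so no visit, measurement or participant is added. The change should be documented before any unblinded comparison of the arms.

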### Inclusion criteria for patients with insomnia

Participants who meet all the following criteria can be enrolled: [1] meeting the diagnostic criteria of ICSD-3 criteria of insomnia [2]; ISI scale score between 8 to 21 [3]; 20 to 45 years old, male or female [4]; HAMD score less than or equal to 17 [5]; not having received any treatments for insomnia for the past month, including medication, and acupuncture [6]; normal result of blood routine [7]; right-handed; and [8] understanding the process of this study and agreeing to participate and sign the consent form.

### Exclusion criteria for patients with insomnia

Participants with any one of the following conditions will be excluded from this trial: [1] experience major depressive disorder, anxiety disorder, panic disorder, or other mental disorders or alcohol or drug addiction [2]; having irregular circadian cycle due to work requirement, [3] insomnia caused by severe pain or other underlying diseases [4]; having problems with communication and unable to perform abdominal rubbing [5]; experience insomnia caused by severe or systemic diseases (endocrine diseases, autoimmune diseases, infectious diseases, diabetes and other metabolic diseases) [6]; had brain surgery or metal implantation ; and [7] pregnant, breast-feeding, or having plans to conceive.

### Withdraw criteria

(1) The participant has an adverse event related to the research.

(2) At the participant’s own request.

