### Outcome measures

To ensure the authenticity of the results, all questionnaires will be conducted by trained independent assessors. Regardless of whether the subjects complete the research project, we will collect the results of all participants. The study schedule (including enrollment, intervention, post-intervention, and follow-up period) is shown in Table 1.

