### Plans to promote participant retention and complete follow-up

To ensure retention of participants, they will be contacted by phone or WeChat 1 day before outcome assessment and will be reimbursed for round-trip travel. Participants have the right to withdraw at any stage of the study. When participants express a desire to withdraw from the study, the researchers will clarified any doubts and inform them of the potential benefits of being in the study. If a participant withdraws from the study, the researcher will try to contact the withdrawn participant to inquire about the reason for the withdrawal, whether there is an AE and outcome assessment.

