### Safety assessments

If the participants experience any discomforts or unexpected situations during the clinical trial, they should inform the researchers immediately, regardless of the causes of these conditions. The researchers will do their best to prevent and treat any possible injuries caused by this study. Important AEs in this study would be qigong exercise-related AEs, such as headache, dizziness or vertigo, distension of head, tinnitus, stuffiness in the chest and worsening shortness of breath, heart-pounding or palpitations, muscular soreness or pain, profuse cold perspiration, irritability, neurasthenia, hallucination and paranoia, and psychological stress. Minor AEs will be treated immediately by the attending TCM doctor. In addition, all severe adverse events will be reported to the Regional Ethics Review Committee of Yueyang Hospital of Integrated Traditional Chinese and Western Medicine affiliated to Shanghai University of Traditional Chinese Medicine within 24 h. If adverse events are determined to be related to the study, the Regional Ethics Review Committee of Yueyang Hospital of Integrated Traditional Chinese and Western Medicine affiliated to Shanghai University of Traditional Chinese Medicine have the right to suspend this study. If an adverse event occurs during the clinical trial, medical experts will be recruited to evaluate and investigate the actual causes and medical and financial compensations will be made to the participant.

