### Statistical analysis

#### Primary outcome analysis

With previous set single blind rule, an independent statistician will analyze the clinical data by SPSS V.24.0 statistical software. Data analysis will be based on the intention-to-treat (ITT) principles. The results of ITT analysis will be compared for consistency. A *p* value < 0.05 will be considered statistically significant. Participants who fail to complete the study will be treated as having no change from baseline at all times in both groups. The Kolmogorov–Smirnov test will be used to test the normality. Appropriate transformations will be applied for non-normal distribution, The continuous variables with normal distribution will be described as mean and standard deviation, while continuous variables with non-normal distribution will be expressed by using median and interquartile interval (IQR), the categorical variable will be expressed in number and proportion.

To compare the baseline characteristics between two groups, Student’s *t* test or Mann–Whitney test will be used for continuous variables. Pearson’s *χ*-squared or Fisher’s exact will be used for categorical variables. To compare the primary and secondary outcomes between groups, continuous data will be tested by Student’s *t* test or non-parametric test. Pearson’s *χ*-squared or Fisher’s exact test will be applied for categorical data at baseline and after intervention. Repeated-measures ANOVA using the group-by-time interaction terms will be used to analyze the between-group differences. Multivariate analysis of variance will be used and the two-two comparisons among the changes in questionnaire scores with repeated measurement times for each group will be done by Bonferroni correction.

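### The no-change rule for non-completers, read literally, overwrites PSQI scores the trial plans to collect, and an unrestricted adverse-event withdrawal criterion can enlarge the group it affects

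*Protocol article*

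**What the plan says.** Four parts of the protocol article bear on this.

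- **Withdraw criteria.** Two are listed. The first is "The participant has an adverse event related to the research"; the second is the participant's own request. The first carries no grade, seriousness or tolerability threshold.
- **Primary outcome analysis.** "Data analysis will be based on the intention-to-treat (ITT) principles". The same paragraph adds: "Participants who fail to complete the study will be treated as having no change from baseline at all times in both groups". Completion is not defined.
- **Outcome measures, and the retention plan.** "Regardless of whether the subjects complete the research project, we will collect the results of all participants". After a withdrawal, the researcher is to try to reach the participant and ask about "the reason for the withdrawal, whether there is an AE and outcome assessment".
- **Safety assessments.** "Important AEs in this study would be qigong exercise-related AEs". The examples run from headache and muscle soreness to hallucination. No matching list is given for CBTI. The section also says: "Minor AEs will be treated immediately by the attending TCM doctor".

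No sentence says that a score actually obtained takes precedence over the no-change rule.

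**The concern.** The collection plan and the analysis rule pull against each other. One gathers week 4, 8 and 12 scores from people who stop; the other scores those people as unchanged at every time point. Taken at its word, the rule would even replace a genuine week 4 score from someone who left in week 6. Setting aside observed post-randomisation outcomes does not fit the stated intention-to-treat principle.

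Most of the harm comes from the analysis rule. The withdrawal criterion matters because it can feed more people into that rule, at a rate that may differ by arm. At stake are the size of the primary PSQI difference and the power to detect it. With unequal loss, the balance between the arms is also at stake.

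**Working it through.** **Inputs from the Sample size calculation section.** Post-treatment PSQI is 8.45 (SD 2.06) for ARQE and 9.92 (SD 2.65) for CBTI. The difference is 9.92 − 8.45 = 1.47. Two-sided alpha is 0.05 and power 0.80. The plan has 51 per group, and then "Considering a 10% loss to follow-up, we aim to recruit 57 patients in each group".

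**Reproducing the plan's figures.** With SD 2.65 in both arms, n = 2 × (1.960 + 0.842)² × 2.65² / 1.47² = 51.01 per group, which matches 51 to rounding. Then 51 / 0.90 = 56.7, so 57. Planned loss is therefore 57 − 51 = 6 per arm.

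**Assumptions the document does not supply.** D is the mean ARQE improvement, taken as 3 or 5 points. CBTI improvement is D − 1.47. Those who stop would have shown their arm's full gain. The numbers scored as no change are a in ARQE and c in CBTI.

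**Formula.** Expected difference = [(57 − a) × D − (57 − c) × (D − 1.47)] / 57.

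Worked cases:
- 6 v 6: 51 × 1.47 / 57 = 1.32, whatever D is.
- 9 v 6, D = 3: (48 × 3 − 51 × 1.53) / 57 = 65.97 / 57 = 1.16.
- 9 v 6, D = 5: (48 × 5 − 51 × 3.53) / 57 = 59.97 / 57 = 1.05.
- 4 v 8, D = 5: (53 × 5 − 49 × 3.53) / 57 = 92.03 / 57 = 1.61.

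Power comes from simulated trials with 57 per arm and a two-sided t test at 0.05. The post-treatment SDs stand in for SDs of change, which is a further assumption. With no loss, power is about 0.91.

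| ARQE v CBTI scored as no change | Difference, D = 3 / D = 5 | Power, D = 3 / D = 5 |
|---|---|---|
| 6 v 6 | 1.32 / 1.32 | 0.85 / 0.79 |
| 7 v 6 | 1.26 / 1.23 | 0.82 / 0.72 |
| 9 v 6 | 1.16 / 1.05 | 0.75 / 0.56 |
| 7 v 5 | 1.24 / 1.17 | 0.80 / 0.67 |
| 6 v 7 | 1.34 / 1.38 | 0.87 / 0.83 |
| 5 v 7 | 1.39 / 1.46 | 0.89 / 0.88 |
| 4 v 8 | 1.47 / 1.61 | 0.93 / 0.94 |

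**When the ARQE effect is overstated.** The formula exceeds 1.47 only if c × (D − 1.47) > a × D, that is, c / a > D / (D − 1.47). The threshold is 3 / 1.53 = 1.96 for D = 3 and 5 / 3.53 = 1.42 for D = 5. A split of 5 v 7 (ratio 1.40) stays below both. A split of 4 v 8 (ratio 2.00) barely passes the first and clearly passes the second.

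**No true difference.** The expected difference becomes (c − a) × D / 57. Equal loss then gives zero bias. A split of 4 v 8 gives a spurious 4 × 3 / 57 = 0.21 or 4 × 5 / 57 = 0.35 in favour of ARQE. A split of 9 v 3 gives 6 × 3 / 57 = 0.32 or 6 × 5 / 57 = 0.53 against it, with a simulated two-sided error rate of about 0.09 or 0.13. At 9 v 6 the error rate stays below 0.05, so a large imbalance is needed.

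**Effect of using the scores.** Take 9 v 6 at D = 5, and suppose the three extra ARQE participants kept half their gain and their scores were analysed. The difference is 1.05 + 3 × 2.5 / 57 = 1.18. If they had returned fully to baseline, their observed scores would give the same 1.05 as the rule.

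**The case against.** The strongest reply is that three readings are stacked: that every related event leads to withdrawal, that those withdrawn count as non-completers, and that the rule overwrites scores in hand. None is spelled out. Prompt treatment of minor events fits with those participants carrying on. The collection plan and the intention-to-treat statement also allow the rule to be read as a fallback for missing scores only, in which case nothing collected is lost. The article is condensed, and operational withdrawal thresholds often sit in the full protocol.

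Much of this stands. It limits how much weight the withdrawal criterion can bear, and it makes the size illustrative. It does not remove the point. The analysis rule is written without an exception, it says it applies at all times, and nothing gives observed scores priority. If the fallback reading is intended, one sentence would settle it.

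Two stronger readings are tempting. A reader might infer that the criterion will certainly cost ARQE more participants. The documents give no event rates, and the listed events include irritability and psychological stress, which are not physically specific to qigong. A reader might also infer that whenever CBTI loses more, the ARQE effect is overstated. The table shows otherwise: 6 v 7 and 5 v 7 both stay below 1.47.

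**Conclusion.** The point holds, with its weight on the analysis rule. As written, the no-change rule discards outcomes the trial means to collect and conflicts with its own intention-to-treat statement. Unequal withdrawal is not required for bias: if a true effect exists and those who stop would have kept their gain, the planned 10% loss alone lowers 1.47 to 1.32. More ARQE loss lowers it further, to 1.16 or 1.05 at 9 v 6. More CBTI loss offsets the shrinkage, and inflates the ARQE effect only with a marked imbalance or when the true difference is small or absent.

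The withdrawal criterion's contribution is real but of unknown size. It depends on event rates, on what completion means, and on whether mild events trigger withdrawal. All the figures rest on an assumed gain of 3 or 5 points, and they shrink as those who stop return towards baseline. The plan should be changed, because the bias is avoidable with data already due to be collected.

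**What to change.** **Main change, in the primary outcome analysis.** Analyse all observed PSQI, ISI, GSRS and HAMD scores by randomised group, whether or not the intervention was stopped. State that the no-change rule never replaces a collected value.

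**Secondary change, in the withdrawal criteria.** Turn criterion (1) into discontinuation of the intervention for related events that are serious, unsafe or intolerable. Keep the week 4, 8 and 12 assessments going for those participants. Reserve withdrawal from the study for withdrawn consent.

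**Cost.** A short amendment to two sections. The assessments are already in the schedule in Table 1, so the only burden is a few more assessment contacts with people who have stopped treatment.
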